### Data analysis

All analyses will be conducted keeping participants in the groups to which they were randomised (intention to treat). We will conduct available data analyses and use multiple imputation with chained equations (with 200 imputed data sets using 30 iterations) to impute missing data for imputed analyses. Both available data and imputed analyses will be used to interpret findings. All models will be estimated using Bayesian inference, with the posterior probability of effect being presented along with posterior medians and 95% compatibility intervals. All models will include an adaptive intercept for each university (multilevel), with standard normal priors.

The primary outcome (PPS) will be standardised and analysed using linear regression, adjusted for age, gender and PPS at baseline. Anxiety, stress, weekly consumption of candy and snacks, and MVPA will be modelled equivalently as PPS. Frequency of heavy episodic drinking, weekly alcohol consumption and weekly consumption of sugary drinks will be analysed using negative binomial regression, adjusted for age, gender and PPS at baseline. Student-t priors will be used for covariate coefficients, normal priors will be used for adaptive intercepts with half-student-t hyperpriors for the SD, and half-student-t priors will also be used for main SDs and dispersion parameters. All student-t priors will have 3 df and a scale of 2.5.

Interaction analyses will be conducted between treatment allocation and age, gender and baseline PPS. Models will be compared using the widely applicable information criterion to decide if interaction models are informative in comparison to non-interaction models.

Attrition analyses will be conducted to investigate systematic differences between responders and non-responders. Logistic regression will be used to estimate the OR of not responding to follow-up with respect to age, gender and baseline PPS. The same priors as the primary analyses will be used.

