### Study setting, recruitment and eligibility

The Focus study will be situated at colleges and universities in Sweden. Students at participating colleges and universities will be invited via email by their university student healthcare to participate in a study, in which they are asked to assess their procrastination. The email contains a hyperlink to a webpage presenting study information and informed consent materials (see online supplemental appendix A). Students who give informed consent will immediately be taken to a web-based questionnaire, which will collect baseline data and check for eligibility. Recruitment will begin in February 2023, and a final dataset will be available by the end of the semester of 2023.

10.1136/bmjopen-2023-072506.supp1Supplementary data

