#### Secondary outcome measures

Anxiety.Stress.Weekly alcohol consumption.Monthly frequency of heavy episodic drinking.Weekly consumption of candy and snacks.Weekly consumption of sugary drinks.Weekly moderate to vigorous physical activity (MVPA).

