### Sample size

The data collected in this trial will be analysed using Bayesian analysis,^33^ which delivers a posterior probability of effect regardless of the number of participants included. We will not use null hypothesis testing; therefore, a traditional power calculation is not required to determine the required sample size to control type I and II errors. Instead, we conducted a Monte Carlo simulation study, assuming a standardised effect of 0.35 Cohen’s d of the intervention on the primary outcome (procrastination behaviour). To at least 80% of the time estimate a posterior probability of effect of at least 95%, the Monte Carlo simulations indicated that data from 1000 participants are required for analysis, meaning that 2000 participants are required to be randomised when assuming a 50% attrition rate. Note that this intervention and trial is novel, and as such there are no previous studies to rely on the determination of effect size. However, a previous study comparing guided and unguided self-help using iCBT with a wait-list control observed effects sizes ranging from 0.5 to 0.7 Cohen’s d.^14^ We anticipate that our brief intervention will be less effective than a full therapy programme, and we have thus assumed a small to medium Cohen’s d of 0.35.

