### Limitations

The trial design necessitates self-assessment of procrastination behaviours among all participants prior to randomisation. Previous research has shown that assessment of behaviours (self-monitoring) may have an effect on self-reported behaviour,^36 37^ thus there is risk of diluting effects by the control group being offered a chance to self-assess their procrastination behaviours. This is, however, unavoidable in order to maintain the naturalistic design of the study and to conduct data collection. Most conservatively, estimated effects may therefore be viewed as caused by the feedback and advice component only, assuming no interaction with self-assessment.

Attrition bias is a concern in digital intervention research, including this study. We are anticipating high attrition at 50%, which is difficult to recover from even using modern methods of imputation. Attrition analyses will reveal if there is evidence of systematic differences among responders and non-responders; however, the study will nevertheless be limited by the risk of attrition bias.

Finally, we have chosen a pragmatic follow-up interval of 2 months. This means that we will not be able to identify earlier effects of the intervention which may have waned.

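### Three count secondary outcomes are adjusted for baseline procrastination but not for their own baseline, and the covariates for the other four secondary outcomes are ambiguous

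*Protocol article*

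**What the plan says.** All of the wording at issue is in the Protocol article, Data analysis.

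- **Primary outcome:** "The primary outcome (PPS) will be standardised and analysed using linear regression, adjusted for age, gender and PPS at baseline". Here the baseline covariate is the outcome's own baseline.
- **Three count outcomes** (heavy episodic drinking, weekly alcohol, sugary drinks): these "will be analysed using negative binomial regression, adjusted for age, gender and PPS at baseline". Own baseline is not listed.
- **Four outcomes modelled as continuous:** "Anxiety, stress, weekly consumption of candy and snacks, and MVPA will be modelled equivalently as PPS". No covariates are named.
- **Interaction and attrition models:** both use age, gender and baseline PPS only.
- **Missing data:** an available-data analysis and a multiply imputed analysis are both used for interpretation. The article does not list the imputation variables.

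On baseline measurement, Study setting, recruitment and eligibility mentions a "web-based questionnaire, which will collect baseline data and check for eligibility". It does not say whether the seven secondary outcomes are among those data. The questionnaires (online appendix B) and the participant timeline (figure 3) are not available here.

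**The concern.** The best single predictor of last week's drinks, or of a current anxiety score, is usually the same measure taken at baseline. Baseline procrastination is at most an indirect proxy. The primary model uses own baseline, but the count models carry over PPS as their only baseline score, so the counterpart of the primary model's strongest covariate is missing.

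The wording for the other four outcomes does not settle the matter. Equivalence to the PPS model can mean the same list of covariates, including baseline PPS. It can also mean the same structure, in which each outcome is adjusted for its own baseline. Two analysts could fit different models and both claim to follow the protocol.

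Precision is at stake for up to seven secondary outcomes. A second, conditional stake is the available-data comparison, because the Limitations section says: "We are anticipating high attrition at 50%, which is difficult to recover from even using modern methods of imputation".

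**Working it through.** **Inputs from the protocol.** Sample size states that "data from 1000 participants are required for analysis, meaning that 2000 participants are required to be randomised when assuming a 50% attrition rate". The inflation step reproduces: 1000 / (1 − 0.5) = 2000. I take 1000 analysed, 500 per arm, as given. Whether that number follows from the assumed d of 0.35 is a separate matter. The plan gives no precision figure for secondary outcomes, so there is nothing further to reproduce.

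**Assumed inputs (none is in the document).** r is the correlation of an outcome's baseline with its follow-up, 0.4 to 0.7. p is the correlation of baseline PPS with the outcome's baseline, 0.2 to 0.4. PPS is taken to relate to follow-up only through the outcome's baseline, so their correlation is r × p. Age, gender and university are ignored.

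**Step 1: precision, standardised continuous outcome.**

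- PPS only: residual variance 1 − (r p)²; SE = √[(1 − (r p)²) × 4/1000].
- Own baseline (with or without PPS): residual variance 1 − r²; SE = √[(1 − r²) × 4/1000].
- Participant multiple = (1 − (r p)²) / (1 − r²).

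| r | SE, PPS only (p = 0.4 to 0.2) | SE, own baseline | SE ratio | Participant multiple |
|---|---|---|---|---|
| 0.4 | 0.0624–0.0630 | 0.0580 | 1.08–1.09 | 1.16–1.18 |
| 0.5 | 0.0620–0.0629 | 0.0548 | 1.13–1.15 | 1.28–1.32 |
| 0.6 | 0.0614–0.0628 | 0.0506 | 1.21–1.24 | 1.47–1.54 |
| 0.7 | 0.0607–0.0626 | 0.0452 | 1.34–1.39 | 1.81–1.92 |

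Extremes: r = 0.4, p = 0.4 gives 0.9744 / 0.84 = 1.16; r = 0.7, p = 0.2 gives 0.9804 / 0.51 = 1.92.

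**Step 2: chance of reaching 95% posterior probability.** With weak priors this is about Φ(δ/SE − 1.645). The protocol gives no effect size for secondary outcomes, so I assume δ = 0.15 SD.

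- PPS only, r = 0.5, p = 0.3: 0.15/0.0625 − 1.645 = 0.755, giving 0.78. At r = 0.7 (SE 0.0618) the result is also 0.78.
- Own baseline, r = 0.5: 0.15/0.0548 − 1.645 = 1.09, giving 0.86.
- Own baseline, r = 0.7: 0.15/0.0452 − 1.645 = 1.67, giving 0.95.

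**Step 3: bias from dropout in the available-data analysis.** Simulation of 600 trials per setting with no true effect, 2000 randomised, 50% response and p = 0.3. The log-odds of responding change by g per SD of own baseline.

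| Dependence of response on own baseline | Bias, PPS only (r = 0.5, 0.6, 0.7) | Bias, own baseline |
|---|---|---|
| None | 0.004, −0.003, 0.002 | within 0.002 |
| Equal in both arms, g = −0.3 | −0.003, −0.001, 0.004 | within 0.003 |
| One arm only, g = −0.25 | −0.056, −0.068, −0.081 | within 0.003 |
| One arm only, g = −0.5 | −0.108, −0.127, −0.150 | within 0.003 |

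A first-order check agrees. At 50% response the responders' mean own baseline shifts by about g/2 in the affected arm, and PPS adjustment removes only the fraction p². The bias is therefore about r(1 − p²)g/2. For r = 0.6 and g = −0.25 this is 0.6 × 0.91 × (−0.125) = −0.068.

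**Limit of the arithmetic.** These figures are for continuous outcomes. The mechanism is the same in a negative binomial model and the gain has the same direction, but I give no size for it.

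**The case against.** **A reader might infer that all seven secondary outcomes omit their own baseline.** The document supports this for three. For the other four, the model they are said to match does adjust for own baseline, so the favourable reading is natural. The PPS-only reading has some support too: the sentence that follows, and the interaction and attrition models, all name PPS as the only baseline score. Neither reading is proved, so the defect for these four is the ambiguity.

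**A reader might infer that the secondary estimates will be biased.** The document does not support that. It anticipates 50% attrition overall and predicts no difference between arms. Step 3 shows essentially no bias under either model when dropout depends on own baseline equally in both arms. The own-baseline model corrects the one-arm scenario because that scenario makes dropout depend on exactly that variable. Imputation might also correct the imputed analysis, and an article commonly leaves the imputation variables to another document. The available-data analysis, which is also used for interpretation, would still be exposed. The protocol already acknowledges attrition bias as a limitation.

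**The gain rests on assumed correlations, and the comparison is valid without it.** Both statements stand. One-week recall of drinks or servings may correlate less strongly over two months than a symptom scale does, which would put the gain at or below the low end. Apart from the dropout scenario, randomisation keeps the comparison fair and only efficiency is lost.

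**The outcomes may not be measured at baseline.** That cannot be checked here. If they are not, own-baseline adjustment is impossible. A reader might then want questions added, but the protocol itself warns that self-assessment can change reported behaviour and stresses low participant burden. The point does not extend to that.

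**Conclusion.** The point holds in a limited form. For the three count outcomes the stated covariates omit own baseline; for the other four secondary outcomes the covariates are not determinable from the text.

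Where own baselines are collected, the cost of adjusting for PPS alone is a standard error about 8% to 39% larger, assuming r of 0.4 to 0.7 in a standardised continuous outcome with 1000 analysed. At an assumed effect of 0.15 SD and r of 0.5 to 0.7, the chance of reaching 95% posterior probability would rise from about 0.78 to between 0.86 and 0.95.

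Protection against dropout bias is a conditional benefit. It applies only if dropout relates to own baseline differently in the two arms, which nothing in the document establishes. The point concerns secondary outcomes only and leaves the primary analysis as it is.

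**What to change.** For each secondary outcome measured at baseline:

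1. State the covariates as age, gender, baseline PPS and the baseline value of that outcome. In the negative binomial models, enter the baseline value suitably transformed, for example as log(baseline + 1).
2. Replace the sentence that ties the four continuous outcomes to the PPS model with this explicit list.
3. Include the same baseline values in the imputation models and in the logistic model for non-response.

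Also say which secondary outcomes the baseline questionnaire contains. Where one is not collected, keep the present covariates for it and say so; adding baseline questions is not part of this change.

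The cost is a few sentences in Data analysis, with no new data and no change to recruitment or to the primary analysis. The choice should be fixed before outcome data are seen.

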### Patient and public involvement

Previous research, interviewing university students about their experiences of health and health-related behaviours, highlighted procrastination and study-related stress as a common barrier for not engaging in healthy routines such as physical activity and healthy cooking.^34^ This study was designed and developed in collaboration with professionals at student healthcare centres across Sweden. During the process of designing the intervention content and usability testing of the digital support, approximately 10 professionals took part in multidisciplinary group meetings during 2022. These meetings defined procrastination in behavioural terms, specified the target behaviour, identified what needs to change, and ways to achieve this using a digital tool.

## Ethics and dissemination

The study was approved by the Swedish Ethical Review Authority on 2022-08-24 (dnr 2022-00353). Students will be asked to give informed consent before participation and after having been given information about the study. The results will be submitted for publication in open-access, peer-reviewed journals.

## Discussion

This RCT aims to estimate the effects of a brief digital procrastination intervention on procrastination behaviours among university students in Sweden. It will add findings on how to support students to overcome procrastination—something that is inadequately evaluated. This is so despite procrastination behaviours being common among university students, and known to cause ill health, distress and negatively impact academic performance.^3 5^ Digital interventions could fulfil these needs and are scalable to a large group of individuals at a low cost. The low cost of delivering digital interventions,^35^ and the low participant burden of completing a brief screening questionnaire, justifies even small effects from the intervention.

### Generalisability

This study is carried out in a college and university setting, reaching students via communication channels used in their academic and daily lives. Students signing up to participate in the study do not represent a population consisting entirely of individuals actively seeking help, and the inclusion criteria are relatively broad for inclusion. The study can, therefore, be understood as an effectiveness trial, which aims to estimate the effects of the intervention in a naturalistic setting. It should be noted that the intervention materials are designed for college and university students, and therefore, generalisability outside the target population is not anticipated. Also, being a student in Sweden is not necessarily comparable to being a student in other countries, and so generalisability to other countries may be limited.

### Limitations

The trial design necessitates self-assessment of procrastination behaviours among all participants prior to randomisation. Previous research has shown that assessment of behaviours (self-monitoring) may have an effect on self-reported behaviour,^36 37^ thus there is risk of diluting effects by the control group being offered a chance to self-assess their procrastination behaviours. This is, however, unavoidable in order to maintain the naturalistic design of the study and to conduct data collection. Most conservatively, estimated effects may therefore be viewed as caused by the feedback and advice component only, assuming no interaction with self-assessment.

Attrition bias is a concern in digital intervention research, including this study. We are anticipating high attrition at 50%, which is difficult to recover from even using modern methods of imputation. Attrition analyses will reveal if there is evidence of systematic differences among responders and non-responders; however, the study will nevertheless be limited by the risk of attrition bias.

Finally, we have chosen a pragmatic follow-up interval of 2 months. This means that we will not be able to identify earlier effects of the intervention which may have waned.

### Public health relevance

Procrastinating affects both physical and mental health negatively and can, apart from increased stress, involve risk behaviours, such as excessive alcohol consumption or tobacco use as stress-relieving strategies. Procrastination behaviour might also out-compete good health habits, such as sleep hygiene, regular physical activity or healthy eating habits, due to high level of stress. By quitting postponing important commitments students increase the chance of succeeding with their studies, decreasing their risk of mental illness, exhaustion and anxiety-related problems. Today, there is a lack of support to help students take control of their procrastination behaviours. Therefor, and due to the high prevalence of procrastination among students, it is valuable to evaluate a scalable digital procrastination support for university students.
